## 19.4 BACKGROUND

### 19.4.1 INTRODUCTION

Coronaviruses are single stranded RNA viruses that are causative for SARS (epidemic in 2003, SARS-CoV), MERS (2012, MERS-CoV) and now COVID-19 (SARS-CoV-2). To date there are no licensed vaccines for SARS, MERS or COVID-19. It is not known what protection might be gained post infection with SARS-CoV-2 and cases of re-infection have been reported [1–5], so it is important that not only a vaccine is developed, but that this can be given safely to boost the immune response in those who have recovered from infection, should this be necessary.

COVAC1 is assessing the safety and immunogenicity of a self-amplifying ribonucleic acid (saRNA) vaccine encoding the S glycoprotein of SARS-CoV-2 and started recruitment in June 2020. At the St Mary's site 37 participants have been recruited and have received a 1 µg dose of saRNA vaccine at Week 0. Around half of these participants have had a previous infection with SARS-CoV-2 and had detectable antibodies against the N-protein (using the Abbott platform) at baseline prior to vaccination. All participants at the St Mary's site have had safety bloods and serum samples taken for analysis of the serological response to the S-protein. However, in order to evaluate the cellular immune responses of these individuals additional blood for peripheral blood mononuclear cells (PBMCs) is needed. This will allow us to explore in detail SARS-CoV-2-specific T- and B- cell immunity post-vaccination over time in those previously infected compared with those naïve to SARS-CoV-2 at baseline.

### 19.4.2 POTENTIAL RISKS AND MITIGATIONS

In this sub-study we require an additional 48 mL of blood for PBMC at five timepoints. This gives a total of an additional 240 mL of blood throughout the duration of the sub-study, and increases the total COVAC1 donation to 415 mL over 1 year, which is within a safe volume for donation and is less than the maximum volume of blood allowed for donation by the blood bank.

The risks to the participant of venepuncture are pain and bruising following the procedure. The participant may also feel faint due to a vaso-vagal response or hypotension, and in this case the venepuncture will cease and the patient will be laid flat until recovery.

### 19.4.3 POTENTIAL BENEFITS

There is no direct benefit to the participants of this sub-study, however a potential benefit is to aid with the understanding of the immune response to the vaccine and any protection this may give.

### 19.4.4 RATIONALE FOR SUB-STUDY

It is not currently known what protection might be gained post natural infection with SARS-CoV-2 but based on findings from other coronaviruses, it is likely that any protection offered will wane with time and that these individuals may benefit from vaccination to boost their immune response. This sub-study will allow us to explore in detail SARS-CoV-2-specific T- and B- cell immunity post-vaccination over time in those previously infected compared with those naïve to SARS-CoV-2 at baseline.

### 19.4.5 OBJECTIVES

The stated objectives, in addition to those of the main study are:

- To explore SARS-CoV-2 vaccine induced cellular immune responses in individuals naïve to SARS-CoV-2

- To explore SARS-CoV-2 vaccine induced cellular immune responses in Individuals recovered from natural SARS-CoV-2 infection
- To compare immune responses to LNP-nCoVsaRNA in those with and without SARS-CoV-2 antibodies at baseline

#### **19.4.6 OUTCOME MEASURES**

These may include but are not limited to cellular and humoral immune responses measured in the following ways:-

- Cell-mediated vaccine-induced immune responses measured by T- cell ELISpot (prior to 2nd vaccination, at 2 weeks post vaccination and at 52 weeks), and memory B-cell ELISpot (prior to 2nd vaccination, at 4 weeks post vaccination and at 52 weeks)
- Cell-mediated vaccine-induced immune responses measured by flow cytometry, activation induced marker assays and intracellular cytokine staining
- B cell receptor sequencing prior to the 2nd vaccination dose, at 1 week post 2nd vaccination dose and at 52 weeks

As humoral immunity is largely being addressed in the main study, this sub-study will focus on measuring cell-mediated immunity to SARS-CoV-2 infection in those receiving the study vaccine.

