### 1.5.4 RATIONALE FOR CHOICE OF TRIAL POPULATION

First-in-human dosing for vaccine candidates is typically in healthy young adult populations as these individuals generate the most robust responses. However, it will be important to demonstrate immunogenicity in those most at risk of severe disease. As this risk increases with age, the upper age limit for the expanded safety evaluation is 75 years, recognising that government guidance on strict social distancing of the over 70 may make it difficult for participants over 70 years old to attend trial sites. All participants will provide samples for immunogenicity assessment, including measurement of titres of serum binding and neutralising antibodies, induction of high levels of which is believed to be essential for an effective vaccine. Thus we will be able to confirm immunogenicity of the vaccine in older participants.

Both male and female participants will be included and trial sites will attempt to keep an equal proportion, although the priority will be to ensure timely accrual to the trial.

In order to study the safety and immunogenicity of LNP-nCoVsaRNA vaccine in individuals with a history of SARS-CoV-2 infection, one investigator site (at St Mary's Hospital, London) will preferentially enrol participants known to have infection-induced SARS-CoV-2 antibodies prior to enrolment. The site's enrolment target is 30 participants.

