## 9.5 ANALYSIS PLAN

A full analysis plan will be provided in a separate Statistical Analysis Plan.

Primary safety analyses will be based on all participants who receive at least one dose of vaccine. Safety endpoints will be compared between the different dose groups. The frequency of adverse events will be tabulated by grade and MedDRA System Organ Class and treatment group, and MedDRA Preferred Term and treatment group. Groups will be compared using Fisher's exact test in terms of the proportion ever experiencing an event in each MedDRA System Organ Class.

Primary analyses of immunological responses at 6 weeks will be based on all participants who receive both the initial vaccination and the booster at 4 weeks. These analyses will exclude participants who are identified as COVID-19 seropositive at baseline (either retrospectively, or those enrolled at the St Mary's Hospital site with known previous SARS-CoV-2 infection). Data will also be censored on participants who acquire SARS-CoV-2 infection (virologically-confirmed) during follow-up or who receive an authorised COVID-19 vaccine.

Immunological responses at all time-points will be compared between the younger and older age groups using cross-sectional analyses and longitudinal multilevel models.

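### Section 9.5 excludes baseline seropositives from the Week 6 analyses but not from the age comparison, where infection-primed titres can confound the age effect

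*Protocol*

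**What the plan says.** Protocol section 9.5 names two immunology analyses.

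- **Primary Week 6 analysis.** It covers participants who had the first vaccination and a booster at 4 weeks. It carries the exclusion: "These analyses will exclude participants who are identified as COVID-19 seropositive at baseline". The exclusion covers seropositives found retrospectively and those enrolled at St Mary's with known infection.
- **Age comparison.** This is a separate paragraph: "Immunological responses at all time-points will be compared between the younger and older age groups", using cross-sectional and longitudinal multilevel models. No exclusion or adjustment for baseline serostatus is stated there.

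Other sections determine who is affected.

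- Section 1.5.4 explains the preferential enrolment at St Mary's: "In order to study the safety and immunogenicity of LNP-nCoVsaRNA vaccine in individuals with a history of SARS-CoV-2 infection".
- Section 19.4.1 reports 37 participants recruited there and says: "Around half of these participants have had a previous infection with SARS-CoV-2".
- Section 3.2 (footnote i) applies the antibody exclusion to cohorts A1, A2, B1 and B2 only. Table 1 gives all four an age range of 18–45. Group C (222 participants, 18–75) has no antibody screen.
- Section 19.4.6 states: "As humoral immunity is largely being addressed in the main study", and on that ground directs the sub-study to cell-mediated immunity.

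**The concern.** The protocol treats infection-primed titres as unsuitable for the Week 6 comparison, but does not carry that restriction to the other immunology analysis it names. Two design features make this matter.

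First, the exclusion does little for the people it singles out. Table 9 puts the second injection of St Mary's sub-study participants at Week 14, so the 4-week-booster condition already removes them from the Week 6 analysis. The age comparison is where they remain.

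Second, serostatus and age are linked by design. Groups A and B are antibody-negative and aged 45 or under. Seropositives come in through Group C, which is also the only source of older participants. If the seropositive share differs between the age groups, part of the apparent age effect is an effect of past infection. It could mimic an age difference or mask a real one. Section 1.5.4 relies on these data to confirm immunogenicity in older participants, so a masked deficit in that group is the outcome to avoid.

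**Working it through.** The protocol states no figure for this point, so there is none to reproduce. The check has two parts: the scope of the text, and the size of the possible bias.

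**Scope.** The opening of the exclusion refers back to the sentence before it, which defines the primary Week 6 analyses. The age comparison follows in its own paragraph, covers all time-points, and neither repeats the exclusion nor names a serostatus term. On its wording, the exclusion does not reach it.

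**Inputs from the protocol**

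- St Mary's participants: 37, about half previously infected (19.4.1). 37/2 = 18.5; 18 is used below.
- Group C: 222 (Table 1). 18/222 = 8.1%.
- SD of log10 IC50: about 1.5 (section 9.3).

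**Assumptions, not in the protocol**

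- Group C splits 111/111 into younger and older.
- Titres in seropositives are 1 to 2 log10 higher.
- Three age splits of the 18: even (9/9), 12/6, and all in one group.

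**Bias.** Bias = shift × (seropositive share in one age group − share in the other).

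| Split of the 18 | Difference in shares | Bias, shift 1 | Bias, shift 2 |
|---|---|---|---|
| 9/9 | 0 | 0 | 0 |
| 12/6 | 6/111 = 0.054 | 0.05 | 0.11 |
| 18/0 | 18/111 = 0.162 | 0.16 | 0.32 |

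The sign is positive or negative according to which age group holds more seropositives.

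**Against the standard error.** SE of the age difference = 1.5 × √(2/111) = 0.201.

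- 12/6 split: 0.27 to 0.54 SE. A nominal two-sided 5% test with no true age effect rejects about 6% to 8% of the time.
- 18/0 split: 0.8 to 1.6 SE. P(|Z + 0.8| > 1.96) = 0.13 and P(|Z + 1.6| > 1.96) = 0.36.

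**Sensitivity to group sizes.** With 74 older and 148 younger participants, and all 18 in the older group, the share difference is 18/74 = 0.243 and the bias 0.24 to 0.49 log10. If the 42 antibody-negative participants given 1 µg in Groups A and B are pooled into a younger group of 111 (making 153), a 9/9 split no longer balances: 9/111 − 9/153 = 0.022, a bias of about 0.02 log10 at a shift of 1.

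**After the fix.** With seropositives excluded, this bias term is zero. With serostatus fitted, it is removed to the extent that the term captures the shift.

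**The case against.** **This is SAP detail.** Section 9.5 defers the full plan to a separate SAP, which is not available here and could restrict or adjust the age models. That is fair for covariates in general. But the protocol itself states an exclusion for seropositives and attaches it to one analysis only, so the gap lies in what the protocol fixes.

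**The exclusion may be meant more widely.** Because St Mary's participants boosted at Week 14 are outside the Week 6 analysis anyway, naming that site suggests a broader intent. That is plausible, and 9.5 nowhere says that seropositives are included in the age comparison. It still leaves the analyst to guess.

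**The bias may be nil and no decision rests on it.** Both limits stand. Equal seropositive shares by age give no bias. Section 1.4.1 bases dose selection on antibody levels at Weeks 2 and 6, not on the age comparison.

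**Two stronger readings are not supported.**

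- A reader might infer that antibody response is never compared by serostatus. Section 19.9.2 plans a seropositive-versus-seronegative comparison of immunological responses with no assay limit. Section 19.4.5 includes the objective "To compare immune responses to LNP-nCoVsaRNA in those with and without SARS-CoV-2 antibodies at baseline". Section 19.4.6 introduces its outcomes with "These may include but are not limited to cellular and humoral immune responses measured in the following ways". The trial summary also has an exploratory objective for vaccinated participants with natural infection. The assays itemised in 19.4.6 are cellular and 9.5 names no titre comparison by serostatus, so saying which section holds it would help, but that is a clarification only.
- A reader might also infer that seropositives were enrolled at other Group C sites. Without an antibody screen this is possible, and 9.5 foresees retrospective identification. But section 19.5 names St Mary's as the only site that recruited antibody-positive participants, and exclusion criterion 3 bars a history of COVID-19 elsewhere.

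**Conclusion.** The concern holds as an avoidable confounder in a non-primary analysis. The seropositive exclusion is tied to the Week 6 analyses and absent from the age comparison, the stated main-study immunology analysis in which Week-14-boosted St Mary's participants remain.

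The size and direction of any bias are unknown, because the protocol gives neither the seropositives' ages nor their titre shift. The figures of 0 to 0.32 log10 rest on 18 seropositives, a 111/111 age split and a shift of 1–2 log10. The upper end needs every seropositive in one age group, and a moderate imbalance barely moves the false-positive rate. The documents therefore support saying that the age effect can be confounded, not that it is. The primary Week 6 comparison is unaffected.

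**What to change.** In section 9.5, do one of the following for the age comparison:

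- apply the same exclusion of baseline seropositives and participants with known prior infection; or
- fit baseline serostatus, taken from the Visit 2 serum, as a term in both the cross-sectional and the multilevel models.

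The change is about one line of text. It needs no new visits or samples, because Table 3 already schedules the Visit 2 serum for all of Group C. Exclusion loses about 18 participants from the age comparison. Fitting serostatus keeps them, but relies on the model to describe the infection-related shift.

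As an optional clarification, state whether 9.5 or 19.9.2 holds the comparison of antibody titres by baseline serostatus.

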#### **19.4.7 STUDY DESIGN**

Participants have already been recruited into COVAC1 at the St Mary's Hospital site and received a 1 µg dose of vaccine. They are due to return at visit 5 for the second dose. Participants that consent to this sub-study will have 48 millilitres of additional blood taken at the following main trial visits: visit 5, visit 6, visit 7, visit 8, visit 11 (Table 9).

### **19.5 SELECTION OF SITES/CLINICIANS**

St Mary's site was chosen as this is the only site where participants who were positive for SARS-CoV-2 antibodies at baseline were recruited. The PI at the site is [name].

### **19.6 SELECTION OF PARTICIPANTS**

Participants will be considered eligible for enrolment in this trial if they fulfil all the inclusion criteria as defined below.

#### **19.6.1 PARTICIPANT INCLUSION CRITERIA**

1. Recruited into COVAC1 at St Mary's site
2. Willing and able to comply with visit schedule and provide samples
3. Able to give informed consent

#### **19.6.2 NUMBER OF PARTICIPANTS**

Maximum 37 participants.

## 19.7 ASSESSMENTS & FOLLOW-UP

The Delegation Log will determine which members of the study team are authorised to conduct the assessments and procedures described in this section.

### 19.7.1 TRIAL ASSESSMENT SCHEDULE

The samples and volumes to be collected are outlined Table 9. The maximum blood volume drawn from a participant who completes 52 weeks of follow-up in the main trial study period, and also participates in the sub-study, is approximately 415 mL. This volume does not include the blood volume that would be required if additional diagnostic tests are needed or safety tests have to be repeated. The total is well within the volumes which are allowed for blood donations in the UK: 470 mL every 16 weeks (females) or every 12 weeks (males).

The main trial visits in the trial assessment schedule requiring additional blood for PBMCs are: 2nd vaccination visit (visit 5; Week 14), weeks 15 (visit 6), Week 16 (visit 7), Week 18 (visit 8) and week 52 (Visit 11).

These main trial visits map to the sub-study timepoints as follows:

| Main COVAC1 Trial Visit | Main COVAC1 Trial Week | Sub-Study Week |
|-------------------------|------------------------|----------------|
| 5                       | 14                     | 0              |
| 6                       | 15                     | 1              |
| 7                       | 16                     | 2              |
| 8                       | 18                     | 4              |
| 11                      | 52                     | 38             |

### 19.7.2 INFORMED CONSENT

Participants will be provided with information about the sub-study in writing. They will have the opportunity to ask questions in person or on the phone.

Key points to communicate during the informed consent process:

- Additional blood is required for 5 of the remaining scheduled site visits.

If they are happy to proceed, they will be asked to indicate their informed consent in writing.

A copy will be provided to the participant and one copy kept in the study file according to local procedures.

### 19.7.3 PROCEDURES FOR ASSESSING IMMUNE RESPONSES

Blood samples will be processed at laboratories at Imperial College London.

#### Cellular immune responses

B and T cellular responses will be assessed through standard immunology techniques, including ELISpot assays, flow cytometry, activation induced marker assays and intracellular cytokine staining.

### 19.7.4 EARLY STOPPING OF FOLLOW-UP

If a participant wishes not to remain in the sub-study they are free to withdraw consent.

Medical data collected in the sub-study will be kept for research purposes and are pseudo-anonymised. Consent for future use of stored samples already collected can be withdrawn when leaving the sub-study early, following a discussion.

#### **19.7.5 LOSS TO FOLLOW-UP**

Study staff will make every effort to contact participants who do not attend their scheduled visits. At least three attempts will be made to contact the participant during the period from enrolment through to Week 52 (Main Trial Visit 11).

Participants who are lost to follow-up after at least three attempts to contact them will be able to return to follow-up if they make contact at a later date before sub-study closure.

#### **19.7.6 COMPLETION OF SUB-STUDY FOLLOW UP**

The sub-study will be closed when all participants have made their final follow-up visit.

## 19.8 DATA MANAGEMENT, RISK ASSESSMENT AND MONITORING

### 19.8.1 DATA MANAGEMENT

MRC CTU will not be responsible for data collection, analysis or reporting of sub-study results. The sub-study will not use the MRC CTU eDC system. Instead, paper CRFs will be used to capture the required data, which will be very limited in scope: demographics, and dates of blood samples. Dates of sub-study blood samples will be entered directly into the paper CRF, which is therefore the source document in this instance. A copy of the CRFs will be provided by the site to Imperial College London. The main data outputs of the study will be directly from laboratory analysers, in the form of Excel files.

### 19.8.2 RISK ASSESSMENT

#### **Safety and Rights of Participants**

The sub-study does not significantly increase the risk to participants in the main COVAC1 trial. Their safety and rights will be safeguarded by processes established in the main COVAC1 trial.

Please see [Section 19.10.2](#) on ethical considerations for the sub-study.

#### **Project Design and Reliability**

The participants in the sub-study will also be participants in the main COVAC1 trial. Participant retention in the main trial has been excellent, and we expect that to continue and be the same for the sub-study.

#### **Project Management and Governance**

The sub-study is part of an Imperial College London PhD project co-supervised by ICL academics with many years of experience of supervising successful PhD projects. The co-supervisors include the COVAC1 CI, [name], and the Scientific Lead, [name]. MRC CTU will not be involved in project management or governance of the sub-study.

### 19.8.3 MONITORING

MRC CTU will not be responsible for monitoring the sub-study. The responsibility for this lies with ICL, and is delegated to the CI – who may delegate this to an appropriately trained member of staff at the Imperial CRF.

All sub-study consent forms will be checked for completeness and for assurance that consent was given before any sub-study blood samples were collected.

100% of the demographics data collected in the CRFs will be verified against source data in the participants' electronic healthcare records.

100% of dates and subject IDs in the outputs from immunology laboratory analyser will be cross-checked against the CRFs for one key cellular immune response analysis.

Monitoring reports will be sent to the sponsor, and to the MRC CTU for addition to the TMF.

#### **Direct Access to Participant Records**

Participating investigators should agree to allow trial-related monitoring, including audits, ethics committee review and regulatory inspections by providing direct access to source data and documents as required. Participants' consent for this was obtained in the main COVAC1 trial consent form.

#### **Confidentiality**

The investigator site and Sponsor must follow the principles of the UK Data Protection Act.

All personal data leaving the investigator site will be pseudo-anonymised in that it will bear the participants' sub-study ID (which will be the same as the main COVAC1 trial ID) and not readily

identifiable information such as name or contact details. The investigator site will maintain a participant identification list which links sub-study IDs to participants' names and NHS numbers.

## **19.9 STATISTICAL CONSIDERATIONS**

### **19.9.1 SAMPLE SIZE**

This sub-study is investigating exploratory outcomes. All participants recruited at St Mary's site will be asked if they wish to participate in this sub-study (n=37).

### **19.9.2 ANALYSIS PLAN**

Immunological responses will be compared between the SARS-CoV-2 seropositive and seronegative participants.

## 19.10 REGULATORY & ETHICAL ISSUES

### 19.10.1 COMPLIANCE

#### Regulatory Compliance

Requirements are equivalent to those for the main COVAC1 trial – see Section 10.1.1. The sub-study will be conducted in compliance with the approved protocol, the Declaration of Helsinki 1996, the principles of Good Clinical Practice (GCP) as laid down by the ICH topic E6 (R2), Commission Clinical Trials Directive 2005/28/EC with the implementation in national legislation in the UK by Statutory Instrument 2004/1031 and subsequent amendments, General Data Protection Regulation and the UK Data Protection Act 2018, and the UK Policy Framework for Health and Social Care Research. This is the

